### 2.8. Statistical Analysis

Statistical analysis will be based on the intention to treat analysis using IBM SPSS Statistics 29 (IBM, Armonk, NY, USA). The Kolmogorov–Smirnov Test will be used to test for normal distribution. Levene’s test will be used to assess the equality of variances between groups. If there is no normal distribution, the Mann–Whitney-U test will be used; otherwise, analysis of variance (ANOVA) will be used to test for differences in the repeated measures of FMAUE (pre, T1, T2, and post). In this 2 × 2 factorial design, group will be the independent factor and time will be the dependent factor. Post hoc analyses will be performed for significant main effects and interactions. One-way ANOVA will be used to ensure that the baseline FMAUE scores before the test are not statistically significant between the two groups. The same analysis will also be performed for KADL, TUG, MAS, and TaS.

For the within-group analysis (pre- and post-test), a paired *t*-test will be used if the distribution is normal; otherwise, the Wilcoxon test will be used.

For FMAUE_Diff_, two-sample *t*-tests will be used to test for the difference between the two groups (rPMS and NMS) if the distribution is normal. If the distribution is not normal, the Wilcoxon test will be used. The same analysis will be used for KADL_Diff_, TUG_Diff_, MAS_Diff_, and TaS_Diff_.

To analyze the relationship between arm spasticity (MAS) and arm function (FMAUE) and independence in ADL (KADL) in each intervention group (rPMS and NMS), correlation analyses between the MAS_total-Diff_ and (TaS_Diff_) and FMAUE_Diff_ as well as KADL_Diff_ will be used.

For missing follow-up measurements, the Last Observation Carried Forward (LOCF) procedure will be applied by inserting the most recent present value before.

The level of statistical significance will be set at *p* < 0.05, and Bonferroni correction will be used for multiple comparisons.

The effect size will be calculated using Cohen’s *d* according to the formula mean difference between two groups divided by the result of the pooled standard deviation (the pooled standard deviation is calculated as (=√[(standard deviation rPMS^2^ + standard deviation NMS^2^)/2])). The effect size will be defined as small (0.2), medium (0.5), or large (0.8) [40].

The primary safety endpoint is the incidence of seizures and headaches during the intervention period.

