### 2.3. Sample Size Calculation

REPMAST is designed to show the superiority of rPMS over NMS. Recently, the effect size of rPMS was calculated to be r = 0.68 for the FMAUE and r = 0.60 for the Wolf Motor Function Test when comparing rPMS with standard therapy [21]. A smaller effect size is expected here, as the comparison between rPMS and NMS contrasts two interventions. As there is still no RCT directly comparing rPMS and NMS, the final sample size was first compared by conducting a feasibility pilot study with 20 patients with stroke (10 in each intervention group) using the same inclusion and exclusion criteria as described above. According to the results of the feasibility pilot study, we found an effect size of 0.6 on FMAUE_Diff_ (the difference between Fugl–Meyer Assessment scores before and after the three-week stimulation session) for the rPMS group. Accordingly, to achieve a 90% statistical power to detect differences in FMAUE_Diff_ between the two groups at the 5% significance level (2-sided), a total sample size of 120 patients is required [25]. With an estimated drop-out rate of 15%, a total sample size of 138 patients (69 in each group) is required for this study.

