### 2.7. Outcome Measures

The primary outcome is the difference between the Fugl–Meyer Assessment for Upper Extremity (FMAUE_Diff_) scores before and after the three-week stimulation session, calculated as follows: FMAUE_Diff_ = (FMAUE_post_ − FMAUE_pre_)/FMAUE_pre_.

The secondary outcomes are KADL, TUG, MAS, and TaS, which are calculated in the same way as the primary outcome of FMAUE_Diff_.

Correlation analyses will be used to analyze the relationship between arm spasticity (MAS and TaS), arm function (FMAUE), and independence in ADL (KADL) in each intervention group (rPMS and NMS). For this reason, a sum score will be calculated for a total MAS score (MAS_total_) of all the muscles assessed. The change in this score (between pre and post, MAS_total-Diff_) and TaS (TaS_Diff_) is correlated with the change in FMAUE (FMAUE_Diff_) as well as with the change in KADL (KADL_Diff_).

For each patient, stimulation and testing will be performed at the same time from Monday to Friday between 09:00 and 12:00.

During the trial, included patients may not be enrolled in other trials, treated with botulinum toxin or antispastic drugs, receive peripheral electrical stimulation, or receive peripheral or central magnetic stimulation (see Figure 2).

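### The repeated-measures analysis of FMAUE is wrongly specified (2 × 2 for four visits, time as the dependent factor, Mann–Whitney fallback) and is not ranked against the two-sample test of FMAUE_Diff

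*Protocol article*

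**What the plan says.** Section 2.7 defines the primary outcome as one number per patient, "FMAUE_Diff_ = (FMAUE_post_ − FMAUE_pre_)/FMAUE_pre". Section 2.3 sizes the trial on that variable, "to achieve a 90% statistical power to detect differences in FMAUE_Diff_ between the two groups at the 5% significance level (2-sided").

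Section 2.8 then gives two between-group analyses of FMAUE.

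- The first is an ANOVA "to test for differences in the repeated measures of FMAUE (pre, T1, T2, and post"), described in these words: "In this 2 × 2 factorial design, group will be the independent factor and time will be the dependent factor". Its alternative is: "If there is no normal distribution, the Mann–Whitney-U test will be used". It continues: "Post hoc analyses will be performed for significant main effects and interactions". This plan is repeated for KADL, TUG, MAS and TaS.
- The second is a two-sample t-test of FMAUE_Diff, or a Wilcoxon test if the data are not normal.

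Neither is labelled primary or supportive. On multiplicity the section says: "The level of statistical significance will be set at *p* < 0.05, and Bonferroni correction will be used for multiple comparisons".

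**The concern.** The description of the ANOVA cannot be carried out as written. Its label does not fit the four visits it lists, its factor roles are wrong, and its fallback answers a different question. An analyst would have to guess the model and the term to be tested, and would have to guess for all five outcomes.

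The unranked pair of analyses adds a second problem. Post hoc tests are triggered by any main effect as well as by the interaction. A time main effect shows only that patients in both arms recover. A group main effect averages in the visit before treatment, so it dilutes any treatment effect. If the routes disagree, the text does not say which one settles superiority.

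**Working it through.** **1. The plan's own figure.** Inputs from section 2.3: effect size 0.6, two-sided 5%, 90% power; 1:1 allocation from section 2.5. The 0.6 is taken as the standardised between-group difference in FMAUE_Diff.

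- Normal approximation: n per arm = 2(1.960 + 1.282)²/0.6² = 58.4, so 59 per arm, 118 in total.
- Two-sample t-test: 59.35, so 60 per arm, 120 in total. This is the stated figure.
- Power at 60 per arm: noncentrality 0.6 × √(60/2) = 3.29 on 118 degrees of freedom, giving 90.3%.

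The sample size therefore belongs to the two-sample comparison of FMAUE_Diff.

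**2. The layout.** Sections 2.4 and 2.8 list pre, T1, T2 and post.

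| | As written | As the listed data require |
|---|---|---|
| Layout | 2 × 2 | 2 groups × 4 visits |
| Dependent variable | time is called the dependent factor | FMAUE |
| Role of time | not a within-patient factor | within-patient factor |
| Group-by-time degrees of freedom | (2−1)(2−1) = 1 | (2−1)(4−1) = 3 |
| Non-normal fallback | Mann–Whitney U | a method for repeated data |

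A true 2 × 2 analysis (pre and post only) would test group-by-time on 1 degree of freedom and would be the t-test of absolute change. The four-visit analysis tests it on 3. These are different tests. Mann–Whitney compares two independent groups on one value per patient. It has no time term, and no visit is named for it.

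**3. Null error if more than one route may count.** For independent tests at 0.05: 1 − 0.95² = 9.75% for two, and 1 − 0.95³ = 14.3% for three. The actual tests are correlated, so null trials were simulated at 60 per arm. The protocol gives no variances, so every distributional input is assumed: baseline centred on 35 (SD 10) or right-skewed; mean gain 6 points, either common to all patients or varying with SD 6; visit error SD 2 or 4. That makes eight scenarios of 3,000 trials each. The FMAUE_Diff test was the t-test, or the rank-sum test when a normality test failed.

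| Rule for success | Null error |
|---|---|
| FMAUE_Diff test alone | 4.3–5.8% |
| Group-by-time alone, Greenhouse–Geisser corrected | 4.3–5.7% |
| Group-by-time alone, uncorrected | 4.9–8.6% |
| FMAUE_Diff or corrected group-by-time | 6.5–9.1% |
| Either of those or the group main effect | 11.4–13.4% |
| FMAUE_Diff or Mann–Whitney at any of T1, T2, post | 10.3–14.5% |
| FMAUE_Diff or corrected group-by-time, each at 0.025 | 3.5–4.6% |

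With another assumed set (baseline 10–55, individual gain mean 6 and SD 7, visit error SD 2.7), FMAUE_Diff or group-by-time gave 10.0% without a sphericity correction and 7.9% with one. Adding the group main effect gave 11.6%, and up to 14% without the correction. A further simulation with the correction gave about 7% and about 10%. Overall: about 6.5–10% for two routes and about 10–14% for three.

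**4. Can the routes disagree?** In that second set, with an assumed true effect of 4.5 points, power was 58% for the t-test of the ratio, 86–89% for group-by-time and 13% for the group main effect. So they can, and often.

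**5. If Bonferroni reached the primary test.** At 60 per arm and effect size 0.6, power is 84.4% at 0.025, and restoring 90% would take 71 per arm (142 evaluable).

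**The case against.** The confirmatory test can be identified without a label. FMAUE_Diff is the declared primary outcome, the trial is powered on it, a two-sample test is assigned to it by name, and 120 reproduces as that test. The ANOVA uses raw FMAUE, which is not the declared primary variable, and nothing says its result can establish superiority. The 2 × 2 label may be loose wording for a two-factor analysis. An article also need not spell out the Bonferroni family or sphericity handling. Most of this stands, and it limits the point. It does not rescue the description itself: the layout, the role of time and the fallback are stated, and stated wrongly.

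Three stronger readings are tempting but not supported.

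- A reader might infer that the trial has no decisive analysis. Sections 2.3 and 2.7 imply one; what is missing is the sentence in section 2.8 that ranks the two.
- A reader might infer that the misdescription inflates false positives. The 2 × 2 and dependent-factor wording does not change the type I error, and a sphericity-corrected interaction test stays near 5%. Inflation needs a rule that any significant test wins uncorrected. The article states no such rule, and it promises Bonferroni.
- A reader might infer that Bonferroni over five outcomes cuts power to about 75% (74.7% at 0.05/5 = 0.01). No section says this, and section 2.3 sets the primary comparison at 5%. Inflation and power loss are also alternatives; they cannot both occur.

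**Conclusion.** Wrong as written, of moderate severity. The errors in the layout, the factor roles and the fallback are certain from the text. They affect FMAUE and, by extension, the four secondary outcomes. Following the stated rule on non-normal data would leave the group-by-time question unanswered.

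The missing ranking is a lesser defect, because the intended confirmatory test can be inferred. Its possible cost is the 6.5–10% or 10–14% null error shown above. Those figures rest on assumed baselines, gains and visit errors, and on no correction being applied across the routes. With FMAUE_Diff alone decisive, the error is about 5% and the planned size is adequate for the stated effect.

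**What to change.** In section 2.8:

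1. State that the between-group comparison of pre-to-post FMAUE is the sole confirmatory test, at two-sided 0.05 and outside the Bonferroni family. The 120 evaluable patients and 90.3% power are kept. Adjusting it for FMAUE_pre, which is already collected, is a free gain. Replacing the ratio as the outcome is a separate decision and is not needed here.
2. Restate the repeated-measures analysis as supportive: 2 (group) × 4 (visit), FMAUE as the dependent variable, visit as a within-patient factor, group-by-visit as the term of interest, fitted as a mixed model or with a sphericity correction. Do the same for the secondary outcomes.
3. Replace the Mann–Whitney fallback for that analysis with a method for repeated data.
4. Confine Bonferroni to the secondary outcomes and the post hoc visit contrasts.

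The cost is protocol wording, with no added patients, visits or data. It should be settled before group allocation is revealed to the analyst.

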### 2.4. Clinical Assessment

Demographic data will be recorded at the measurement time point ‘pre’ before the intervention. Imaging data are used to determine the territory affected by the stroke. This will be followed by a medical history and a physical and neurological examination.

The following scales will be used to quantify neurological deficits, as assessed by trained raters before the intervention (‘pre’), at the end of the first week (T1), at the end of the second week (T2), and at the end (‘post’) of the three-week stimulation session: the Fugl–Meyer Assessment for Upper Extremity (FMAUE), an index to assess the sensorimotor impairment; the Katz Index of Independence in Activities of Daily Living (KADL) for the independence in activities of daily living (ADL); the Timed Up and Go Test (TUG) to measure mobility [26]; and the Modified Ashworth Scale (MAS) [27] and Tardieu Scale (TaS) [28] for spasticity.

The Fugl–Meyer Assessment for Upper Extremity (FMAUE) consists of 33 items with a maximum score of 66. Each item is scored on a 3-point scale of 0 points (unable to perform), 1 point (partially able to perform), and 2 points (fully able to perform). The FMAUE includes the following assessment categories: shoulder–elbow–forearm function, wrist function, hand function (subscore C), and coordination/speed [29]. The FMAUE generally has a very high inter-rater reliability, especially the subscale for upper extremity motor skills, which is used in this study [30,31,32]. This test also shows high sensitivity for patients with severe to moderate impairment [29].

The Katz Index of Independence in Activities of Daily Living (KADL) assesses the ability to perform ADLs independently in six functions, including bathing, dressing, toileting, transferring, continence, and feeding. Patients score ‘yes’ or ‘no’ for independence in each of the six functions. A score of 6 indicates full function, 4 indicates moderate impairment, and 2 or less indicates severe functional impairment [33]. The KADL has an excellent intra-rater reliability (intercorrelation coefficient, ICC= 1.000) and internal validity (ICC = 0.999) [34].

To measure mobility, the change in time for the Timed Up and Go Test (TUG) will be assessed [26]. The TUG measures the time taken for a patient to get up from an armchair, walk 3 meters, turn around, walk back, and sit down again [26]. This widely used and well-known test has very good inter- and intra-rater reliability (ICC = 0.99) [26].

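### LOCF freezes drop-outs while both arms are still recovering: a modest shrinkage if the arms lose patients equally, a bias in either direction if they do not

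*Protocol article*

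**What the plan says.** Section 2.8 names one method for missing follow-up scores: "For missing follow-up measurements, the Last Observation Carried Forward (LOCF) procedure will be applied by inserting the most recent present value before". It is applied under intention to treat ("Statistical analysis will be based on the intention to treat analysis"), so drop-outs enter the primary comparison with carried-forward values.

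The primary outcome (section 2.7) is the pre-to-post change in FMAUE divided by the pre score. For its between-group comparison, section 2.8 states that "two-sample *t*-tests will be used to test for the difference between the two groups (rPMS and NMS) if the distribution is normal", with a rank test otherwise.

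FMAUE is measured before treatment, at the end of weeks 1 and 2 (T1, T2) and at the end of week 3 (section 2.4). Section 2.8 also plans an ANOVA over all four visits.

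Section 2.3 allows for loss: "With an estimated drop-out rate of 15"%. No split by arm and no timing is given. Eligibility is stroke within six months (section 2.2), and stimulation is added to standard rehabilitation in both arms (Abstract).

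**The concern.** LOCF is unbiased only if scores would have stayed flat after the last visit, or if the errors cancel between arms. Flat scores are implausible here, because the patients are subacute, both arms are rehabilitated and stimulated, and the endpoint itself is improvement.

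A patient lost before T1 receives FMAUE_Diff = 0, and one lost after T1 keeps the week 1 value. The test treats these as observed, and the four-visit ANOVA inherits the same flattened curves. At 15%, about 21 of 138 patients are affected (0.15 x 138 = 20.7).

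At stake are the size of the primary estimate and, if the arms lose patients unequally, the type I error of a superiority trial.

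**Working it through.** **The plan's own figure.** With d = 0.6, two-sided 5% and 90% power, the noncentral t gives 60 per arm, 120 in total (power 90.3%). The 138 is 120 x 1.15. The figure reproduces when 0.6 is read as a between-group standardised difference. With 69 per arm and nothing missing, power would be 93.8%.

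**Inputs.** From the documents: effect 0.60 SD, 69 per arm, 15% drop-out, visits at weeks 1, 2 and 3. Assumed, because the documents do not give them: common recovery R of 0.5, 1.0 or 1.5 SD of the change; linear recovery; loss spread evenly over the three weeks; and the split by arm. Dividing a patient's change by a fixed baseline does not alter the share accrued at each visit, so the closed form below also applies to relative change.

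**Bias formula.** Let p be the drop-out proportion and U the mean recovery not yet accrued among drop-outs:

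bias = -(p_rPMS x U_rPMS - p_NMS x U_NMS)

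With evenly spread loss, the mean share accrued at the last visit is (0 + 1/3 + 2/3)/3 = 1/3. So U_NMS = (2/3)R and U_rPMS = (2/3)(R + 0.60).

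**Equal 15% loss.** R cancels. The share retained is 0.85 + 0.05 x (0 + 1/3 + 2/3) = 0.90, so 0.60 becomes 0.54. If all are lost before T1, 0.85 is retained (0.51). If all are lost after T2, 0.95 is retained (0.57).

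**Unequal loss, true effect 0.60, R = 1.**
- rPMS 20%, NMS 10%: 0.60 - (2/3)(0.20 x 1.6 - 0.10 x 1) = 0.45
- rPMS 25%, NMS 5%: 0.60 - (2/3)(0.25 x 1.6 - 0.05 x 1) = 0.37
- rPMS 5%, NMS 25%: 0.60 - (2/3)(0.05 x 1.6 - 0.25 x 1) = 0.71

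**Unequal loss, no true effect.** Bias = -(2/3) x R x (p_rPMS - p_NMS). At 20% against 10% it is -0.03, -0.07 and -0.10 SD for R = 0.5, 1.0 and 1.5. At 25% against 5% it is -0.07, -0.13 and -0.20 SD.

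**Simulation.** 3,000 trials per scenario, 69 per arm, normal outcomes, loss unrelated to scores. LOCF with a t-test is compared with an unstructured-covariance mixed model on T1, T2 and post. The three values in a cell are for R = 0.5 / 1.0 / 1.5.

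| True effect | Drop-out NMS / rPMS | LOCF estimate (SD) | LOCF rejects | Mixed model rejects |
|---|---|---|---|---|
| 0.60 | 15% / 15% | 0.54 / 0.53 / 0.54 | 90.0 / 86.9 / 84.2% | 91.6 / 90.4 / 91.0% |
| 0.60 | 10% / 20% | 0.48 / 0.45 / 0.42 | 82.2 / 73.9 / 62.2% | 91.2 / 91.8 / 92.1% |
| 0.60 | 5% / 25% | 0.42 / 0.36 / 0.29 | 71.1 / 52.5 / 33.4% | 90.5 / 91.4 / 90.4% |
| 0.60 | 25% / 5% | 0.65 / 0.71 / 0.79 | 97.6 / 98.7 / 99.4% | 90.7 / 90.0 / 91.1% |
| 0 | 15% / 15% | -0.01 / 0.00 / 0.00 | 4.5 / 5.4 / 4.7% | 4.6 / 5.1 / 4.9% |
| 0 | 10% / 20% | -0.03 / -0.07 / -0.10 | 5.0 / 7.3 / 9.3% | 4.6 / 5.5 / 4.7% |
| 0 | 5% / 25% | -0.07 / -0.14 / -0.21 | 7.6 / 13.9 / 22.3% | 5.5 / 5.2 / 4.8% |

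The estimates agree with the closed form. With no true effect, swapping the arms reverses the sign of the bias and leaves the error rate unchanged.

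**Loss that depends on earlier weekly scores (R = 1).** With no effect and a nominal 5% / 25% split, type I error was 16.5% for LOCF, 16.1% for completers only (estimate +0.19 SD) and 5.0% for the mixed model. With a true 0.60 and a nominal 15% in each arm, power was 80.0% for LOCF and 89.3% for the mixed model.

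**The case against.** The strongest reply is that the only documented drop-out figure is an overall 15%, and that equal loss at that rate does little harm: about a tenth of the effect is lost, and type I error stays at 4.5-5.4%. Patients are inpatients treated for three weeks, and section 2.6.2 applies the same two intensity criteria to NMS as to rPMS. All of this stands, and it limits the point.

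A reader might infer three stronger claims, which the documents do not support:

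- **That the trial as planned has an inflated false-positive rate.** This follows only if the arms lose patients unequally, and nothing says that they will. Section 2.6.1 excludes patients who cannot tolerate sufficient rPMS intensity, and section 2.6.2 has no matching sentence. The timing of that exclusion relative to randomisation is not stated, so it makes unequal loss possible and no more. The two sections should be reconciled with each other and with intention to treat.
- **That LOCF always shrinks the effect and is therefore a safe, conservative choice.** Heavier NMS loss can inflate it: 0.60 becomes 0.71 at 25% NMS against 5% rPMS with R = 1.
- **That the lack of a sensitivity analysis is itself a defect.** A condensed article may leave that to a fuller document.

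It is also fair to say that the mixed model does well because the simulated data meet its missing-at-random assumption. No scenario with data missing not at random was run. The power and type I figures use normal outcomes, and relative change may be skewed.

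**Conclusion.** The point holds as a criticism of a stated choice. LOCF assumes no further change in patients who are expected to keep improving, and it is the only method named.

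At equal 15% drop-out the cost is modest: 0.60 SD becomes about 0.54 (0.51 to 0.57), and power is about 84-90% against 90-92% when loss is unrelated to scores. The more serious risk is conditional on unequal loss. With no true effect, type I error is about 5-9% at 10% against 20%, and about 8-22% at 5% against 25%. The direction depends on which arm loses more.

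The mechanism follows from the design. The sizes rest on assumed recovery, linearity, timing and split, and should be read as ranges. The change should be made, because a better method is available from data already scheduled.

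**What to change.** Replace LOCF in the primary analysis by a likelihood-based mixed model for repeated measures. The outcome is change from pre divided by pre at T1, T2 and post. The terms are group, visit, group x visit and FMAUE_pre, with unstructured covariance, and the primary contrast is the group difference at post. If the sponsor prefers raw FMAUE, the endpoint in section 2.7 must be changed to match and the sample size re-checked, since the 0.6 in section 2.3 is on FMAUE_Diff.

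Patients with no post-baseline score contribute no outcome record to this model, so it does not by itself cover all randomised patients. Choose one of these:
- multiple imputation by arm for all randomised patients; or
- a constrained longitudinal model on raw FMAUE with pre as one of the outcomes. This needs the raw scale, because relative change at pre is zero by definition.

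Both the model and standard imputation assume data missing at random, so keep one delta-adjusted analysis as a sensitivity check. Completers only is not a substitute.

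The cost is revised wording in section 2.8 (including the rank-test fallback, which has no direct counterpart in the model), slightly more analysis work and reliance on missing at random. T1 and T2 are already collected and the planned software fits mixed models. Section 2.5 keeps the analyst unaware of allocation, so the change can be made blind.
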